#### Phase 1: baseline measurement, determining barriers and providing performance feedback

The objective of the first phase is to provide centre-specific performance feedback to all participating hospitals, based on their local baseline measurement. Furthermore, this phase enables us to identify best practices, additional local barriers and local opportunities. The Dutch-TIMELINESS project will retrospectively analyse all patients that underwent ERCP for choledocholithiasis in the period between 1 January 2023 and 31 March 2023. Data regarding patient, treatment and outcome characteristics will be extracted from the patient’s electronic health record. Frailty will be measured using the validated modified Frailty Index-5 (mFI-5).^25^ We decided on using this frailty index as it was proven a strong predictor of mortality and postoperative complications in geriatric patients undergoing cholecystectomy.^26^

The data collection in phase 1 will be executed conform the Snapshot method.^27^ The Dutch Snapshot Research Group (DSRG) is a Dutch surgical network that facilitates research collaboration in the Netherlands, initiated in 2014. The Snapshot research method is collaborative research with the aim of easily collecting data from multiple hospitals, with help from residents in each centre. For that reason, the approval of the DSRG was obtained prior to the start of the Dutch-TIMELINESS. For this first phase, data has been collected since February 2025. The timing of data completion differed across participating centres, with some centres completing their registrations earlier than others.

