#### Phase 2: engaging local stakeholders and establishing tailored guidelines

The objective of this second phase is to establish a tailored protocol for the treatment of choledocholithiasis in each participating hospital. First, the participating hospitals will receive performance feedback based on their baseline measurement. This feedback will contain the local percentage of guideline adherence compared with the average results and best practices. The hospitals that perform best will be asked to share their protocols and policies around choledocholithiasis. The summary provided to each hospital will also include their own essential data needed for logistics, such as the mean number of patients per week, the number of referred patients, the success rate of the ERCP and the time between diagnosis and ERCP. The latter may be key, as proper planning and teamwork between gastroenterologist and surgeon from diagnosis onwards will buy valuable time. Second, guided by the summarised data, local barriers and determinants of success will be found. Each hospital will gather their local stakeholders. These stakeholders will at least consist of the gastrointestinal surgeons, gastroenterologists and anaesthesiologists. Together, they will establish a local, tailored guideline. All parties involved will be informed by the local investigators and will be actively included in the process.

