In phase 3, all patients 18 years or older diagnosed with choledocholithiasis, with a gallbladder in situ, who will undergo ERCP in the period between 1 December 2025 and 31 March 2026, will be included. This period was chosen to match the calendar quarter used in phase 1. December will be used as a wash-in period to separate the start-up effects from the true effect of the implementation. Data from this period will be excluded from the analysis to minimise bias from partial adoption of the local protocol. The follow-up period for phase 3 will be 8 weeks from the date of ERCP, to ensure more complete data on elective cholecystectomies and postoperative complications. A prolonged follow-up is not required as the primary aim of this phase is to evaluate the implementation process rather than long-term outcomes.

For the primary analysis, the population will be defined identically in both phases. All eligible patients with a gallbladder in situ who underwent a first successful ERCP for choledocholithiasis within the predefined inclusion window. Patients who are not candidates for cholecystectomy due to surgical contraindications will be excluded from the analysis. These surgical contraindications include absolute contraindications for general anaesthesia (such as haemodynamic instability or extensive comorbidities) as determined by the attending anaesthesiologist, liver cirrhosis, loco-regional malignancy, gallbladder fistula and extensive or complicated previous abdominal surgery. These patients will be recorded in the database but excluded from outcome analysis. Patients who decline cholecystectomy or are advised against cholecystectomy for non-surgical reasons will remain included. Patients who are transferred will be registered in the hospital where the successful ERCP was performed. Patients who are transferred solely for cholecystectomy will also be registered under the ERCP hospital. This approach ensures that the primary endpoint is evaluated in comparable populations in both periods.

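### The primary denominator excludes patients on a clinician judgement without a threshold, ascertained differently in 2023 and 2026, so comparability is not ensured and the 85% target is sensitive to it

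*Protocol article*

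**What the plan says.** The section Targeted sites, population and eligibility criteria states: "For the primary analysis, the population will be defined identically in both phases". It then removes patients judged not to be candidates for surgery. One ground is "absolute contraindications for general anaesthesia (such as haemodynamic instability or extensive comorbidities) as determined by the attending anaesthesiologist". Others are liver cirrhosis, loco-regional malignancy, gallbladder fistula, and major or complicated earlier abdominal surgery. Of those removed it says: "These patients will be recorded in the database but excluded from outcome analysis". A neighbouring group is kept: "Patients who decline cholecystectomy or are advised against cholecystectomy for non-surgical reasons will remain included". The paragraph closes with an assurance: "This approach ensures that the primary endpoint is evaluated in comparable populations in both periods".

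The two periods are ascertained differently. For phase 1: "The Dutch-TIMELINESS project will retrospectively analyse all patients that underwent ERCP for choledocholithiasis in the period between 1 January 2023 and 31 March 2023". Those data "will be extracted from the patient’s electronic health record", with residents helping in each centre. In phase 3 local investigators include patients prospectively. Between the two, each hospital receives performance feedback and writes a local guideline with its stakeholders: "These stakeholders will at least consist of the gastrointestinal surgeons, gastroenterologists and anaesthesiologists".

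The section Primary objectives' statistical plan specifies a mixed-effects logistic model adjusted for case mix. It lists three sensitivity analyses: complete case, unadjusted, and hospital-level paired. It also reports the proportion of hospitals reaching 85%.

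**The concern.** The examples given for the anaesthetic criterion set no cut-off, and neither does the wording on earlier abdominal surgery. Two clinicians, or one record abstractor and one prospective investigator, could classify the same patient differently. The recorded reason then decides whether an unoperated patient counts. A surgical contraindication removes the patient. A refusal, or advice against surgery on non-surgical grounds, leaves the patient in as non-adherent.

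Someone operated on within 72 hours was evidently accepted for anaesthesia and surgery, so those excluded are almost all non-adherent. Any wrongly excluded patient therefore raises the displayed rate. According to the Sample size section, the primary aim is to estimate national adherence around the 85% target. At stake is whether a reported 85%, nationally or in one hospital, reflects care delivered or partly reflects who was removed from the denominator.

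**Working it through.** **Inputs from the Sample size section:** baseline about 10%, target 85%, 35 patients per hospital, 61 hospitals, 2135 patients per period, 10% non-inclusion, intracluster correlation 0.10, half-width 3.4 points.

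**Not in the documents, so assumed:** the share excluded in each period (0 to 20% explored), and adherence before exclusion (values near the target).

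**Step 1. The plan's own precision figure.**
- Design effect = 1 + (35 − 1) × 0.10 = 4.40.
- n per period = 2135 × 0.9 = 1921.5.
- Half-width = 1.96 × √(0.85 × 0.15 × 4.40 / 1921.5) = 0.0335, or 3.35 points. This agrees with the stated 3.4.

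**Step 2. Effect of exclusions.** Let p be adherence before the exclusion in question and e the share of those patients removed, all non-adherent. Displayed adherence = p/(1 − e).

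| p | e = 5% | e = 10% | e = 20% |
|---|---|---|---|
| 10% | 10.5% | 11.1% | 12.5% |
| 75% | 78.9% | 83.3% | 93.8% |
| 80% | 84.2% | 88.9% | 100% |

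**Step 3. Share needed to display 85%,** e = 1 − p/0.85:
- p = 75%: 1 − 0.75/0.85 = 11.8%.
- p = 80%: 1 − 0.80/0.85 = 5.9%.
- p = 81.6%: 1 − 0.816/0.85 = 4.0%. The shift of 85 − 81.6 = 3.4 points equals the whole stated half-width.
- p = 10%: 1 − 0.10/0.85 = 88.2%. Exclusions on that scale are not credible.

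**Step 4. One hospital.** With 35 patients, 29 adherent is 29/35 = 82.9%. Removing one non-adherent patient gives 29/34 = 85.3%, which crosses the target.

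**Step 5. The before-after difference.** Take 10% in 2023 with no wrong exclusions, and 80% in 2026 with 10% wrongly excluded. The difference shown is 88.9 − 10 = 78.9 points instead of 70. Its size changes by 8.9 points, but the existence of a large rise does not depend on this.

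**Step 6. What the planned analyses can do.** The case-mix model is fitted to patients who remain after exclusion. Adjusting for ASA class, frailty index, age and the rest can remove part of a case-mix difference between the periods. It cannot bring removed patients back or correct crude rates set against 85%. None of the three listed sensitivity analyses is described as restoring them.

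**The case against.** The strongest reply is that the estimand is surgical candidates, so properly excluded patients cause no bias. Only misclassified ones do, and no documented figure gives their number. That stands: the shares above are assumptions, and the formula shows sensitivity, not an estimate of bias.

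There are real safeguards. The anaesthetic criterion is limited to absolute contraindications. Cirrhosis, malignancy and fistula are diagnoses that can be read from a record. Refusals stay in, excluded patients are recorded, and the model adjusts for likely drivers of exclusion. These reduce the problem, but they do not justify saying that comparability is ensured.

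The direction is not fixed either. Phase 1 data have been collected since February 2025, within the project, so 2023 abstractors also work with knowledge of its aim. They could label unoperated patients as contraindicated, which would raise 2023 adherence. The low baseline limits this: even 20% excluded moves 10% only to 12.5%.

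Two stronger readings are tempting:
- **That the anaesthesiologist's judgement is seldom on file for 2023.** The article does not say so. The 10% is a survey estimate of surgery within 72 hours. The remaining patients are not early, which is not the same as never operated on or never assessed.
- **That this judgement is built into the 2026 care pathway.** The article makes anaesthesiologists co-authors of the local guideline and states no assessment of each patient.

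The point needs neither claim. It is enough that an open-ended judgement is read from records in one period and recorded prospectively in the other.

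**Conclusion.** The concern holds in a limited form. Comparability of the two populations is asserted but not secured, and no listed analysis tests it. The consequence falls mainly on the 85% target. With adherence near 80%, wrong exclusion of about 4 to 6% of patients moves the displayed rate by as much as the stated precision or more, and in a hospital of 35 a single patient can matter. This rests on assumed shares and on the excluded patients being non-adherent. If some were adherent, the shift would be smaller.

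A reader might infer that the populations are shown to be non-comparable, or that exclusions could manufacture the improvement. The documents support neither: going from 10% to 85% by exclusion alone would need 88% of patients removed. Nor are 5.9% and 11.8% differences in exclusion between periods. They are 2026 shares, solved backwards from 85%, and do not depend on what was excluded in 2023.

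**What to change.** 1. Add a prespecified sensitivity analysis, reported beside the primary one. It should include all patients with a gallbladder in situ and a first successful ERCP in both periods, without the contraindication exclusion. It should cover national adherence, the period difference, and the proportion of hospitals reaching 85%.
2. Report the number and share excluded by reason, period and hospital.
3. Replace the closing assurance with a statement that comparability is intended and will be examined through items 1 and 2.

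The primary population can stay as it is. Counting patients later judged unfit as non-adherent in the primary analysis would change the estimand and is not needed to answer this point.

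The cost is mostly wording, because excluded patients are already recorded. The article does not say that their 72-hour outcome is captured, so this must be confirmed, with retrieval where it is missing. All-patient adherence will be lower and will include patients unfit for surgery, so it should be read as a check on the primary result and not as a replacement for it. The change should be settled before the 2026 data are analysed.

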### Sample size

Dutch-TIMELINESS is a national implementation project rather than a conventional trial designed primarily to test a treatment-effect hypothesis. Because the expected difference is large, a conventional superiority calculation comparing the increase from approximately 10% to 85% would require only seven patients (two-sided alpha of 0.05 and a power of 0.80). If this minimum number were applied to each of the 61 participating hospitals, this would correspond to 427 patients per period. However, this calculation is mainly illustrative, as the primary aim is the national estimation of adherence around the predefined implementation target.

In 2023, a total of 9389 ERCP procedures for choledocholithiasis were recorded in the Netherlands.^29^ These were performed on 8545 unique patients, indicating that some underwent multiple ERCPs. With 61 hospitals participating, 3 months of data collection is expected to yield 35 patients per hospital (2135 patients in total). Within a total of two periods, assuming an anticipated 10% non-inclusion, the project is expected to include approximately 3843 patients. With an average cluster size of 35 patients, and an assumed intracluster correlation coefficient of 0.10, the design effect is 4.40. At an expected post implementation adherence of 85%, this allows estimation of national adherence with a 95% CI of approximately 85%±3.4 percentage points. The planned sample provides sufficient precision to estimate adherence around the predefined implementation target, supports hospital-level benchmarking and allows for adjusted analyses accounting for clustering and case mix.

### Patient and public involvement statement

The Nederlandse Leverpatiënten Vereniging (Dutch Liver Patient Association) was involved from study design onwards. They were asked to ensure patient perspective and contribute to the development of centralised patient information. They shared their thoughts during the project concept presentation and gave feedback on the trial protocol. Their input confirmed that the Dutch-TIMELINESS project is relevant for patients.

## Outcome measures and predefined statistical analysis plan

### General principles

The gathered data during phase 1 and phase 3 will be stored and managed using REDCap electronic data capture tools.^30
31^ Data analyses will be performed using the latest version of RStudio.^32^ Data will be checked for inconsistencies and missing values, which will be corrected or retrieved when possible. If necessary, missing data will be imputed using multiple imputation. Descriptive categorical data will be presented as counts and percentages. Categorical variables will be analysed using the χ^2^ test or Fisher’s exact test. Continuous data will be presented with means, SD and percentiles. Where appropriate, comparisons will be made using Mann-Whitney U tests, Kruskal-Wallis tests, t-tests or analysis of variance.

### Primary objectives’ statistical plan

To determine whether this implementation project has improved guideline adherence, we will perform a before-and-after analysis as previously described in the methods section. The primary outcome measure is adherence to the Dutch National Guideline ‘Gallstone disease’,^4^ defined as the proportion of patients undergoing cholecystectomy within 72 hours after successful ERCP. These percentages will be reported per hospital (anonymously) and as national mean. The results will be depicted using a slope chart showing the change in guideline adherence per hospital between the two time points we will compare: January to March 2023 versus January to March 2026. The proportion of hospitals reaching the predefined 85% adherence target will also be reported.

Due to the non-randomised nature of this project, we expect differences in baseline characteristics between hospitals and time periods. The primary statistical analysis will use a mixed-effects logistic regression model fitted at patient level. Period defined as year 2023 versus 2026 will be included as the fixed effect of primary interest. To adjust for case-mix, prespecified variables will be included as fixed effects. These include: age, body mass index, American Society of Anaesthesiologists classification, history of biliary disease, history of abdominal surgery, use of anticoagulation, use of immunosuppressants, mFI-5 score and dementia. A random intercept per hospital will account for clustering. To improve clinical interpretability, marginal model-based adjusted adherence rates for each period and the adjusted absolute difference in adherence between periods will also be derived from the mixed-effects model and reported with 95% CIs.

Missing data will be handled using multiple imputation under the assumption of missing-at-random. The imputation model will include the outcome, period, hospital, all variables included in the analysis model. The number of imputations will be at least 20. Estimates will be pooled according to Rubin’s rules. Prespecified sensitivity analysis will include: a complete case analysis, an unadjusted mixed-effects model including period as the only fixed effect, a hospital-level paired analysis in which the change in adherence is calculated for each hospital and summarised nationally.

During the process of project design, several questions of scientific interest were encountered that will be addressed, using the data generated by the Dutch-TIMELINESS project. These predefined secondary objectives, along with a brief plan for their analysis, are presented in online supplemental file 1. These secondary objectives include:

To determine the effect of the time between diagnosis of choledocholithiasis and ERCP on morbidity, the success rate of the first ERCP, complications during ERCP and post-ERCP.To determine the effect of the time between ERCP and cholecystectomy on morbidity and surgical complications.To determine whether frailty modifies the association between cholecystectomy within or after 72 hours and morbidity in frail patients.To determine whether gallstones on preoperative imaging are associated with recurrent biliary events before cholecystectomy and with the presence of intraoperative gallbladder stones.To compare national hospital-level healthcare costs before and after the Dutch-TIMELINESS project.To evaluate the adoption, implementation and maintenance of the Dutch guidelines following the Dutch-TIMELINESS project.

Strengths and limitations of this studyNational coverage: participation of all centres in the Netherlands performing endoscopic retrograde cholangiopancreatography for choledocholithiasis.The phased implementation strategy benchmarks current practice, customises protocols and evaluates results to enable local changes while following national guidelines.Before-after design: system changes over time might influence adherence independent of the intervention.Selection bias: non-participation in the prospective phase might lead to potential selection.Information bias: in the retrospective phase, loss to follow-up might occur.

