**Methods and analysis:**

The Dutch-TIMELINESS is a multicentre implementation project using a Multiphase Optimisation Strategy. The project includes 61 Dutch hospitals. In phase 1, all patients undergoing ERCP for choledocholithiasis from 1 January to 31 March 2023 will be analysed to serve as a benchmark. In phase 2, each hospital develops and implements its own tailored protocol in line with the guideline, guided by the benchmark data. In phase 3, from 1 December 2025 to 31 March 2026, the new protocols will be prospectively evaluated with real-time monitoring and refined as necessary. Statistical methods are predefined in the protocol.

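### The primary model's only random effect is a hospital intercept, so if hospitals' log-odds changes differ, its 95% CIs for the before-after effect are too narrow

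*Protocol article*

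**What the plan says.** The Protocol article, under Primary objectives' statistical plan, fixes the model: "The primary statistical analysis will use a mixed-effects logistic regression model fitted at patient level". On the effect it says "Period defined as year 2023 versus 2026 will be included as the fixed effect of primary interest", and on the random part "A random intercept per hospital will account for clustering". Case-mix variables enter as fixed effects. The reported quantities come from the same fit: adjusted rates per period, and "the adjusted absolute difference in adherence between periods will also be derived from the mixed-effects model and reported with 95% CIs". That section names no hospital-by-period term, random slope or cluster-robust variance.

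Three other statements bear on this:

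- In the Abstract, Methods and analysis: "each hospital develops and implements its own tailored protocol in line with the guideline". The Phase 2 and Phase 3 sections add that local barriers shape this protocol and that it may be adjusted every 4 weeks.
- The statistical plan will show a "slope chart showing the change in guideline adherence per hospital" and lists, as a sensitivity analysis, "a hospital-level paired analysis in which the change in adherence is calculated for each hospital and summarised nationally".
- The Sample size section inflates the variance for clustering: "an assumed intracluster correlation coefficient of 0.10, the design effect is 4.40".

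**The concern.** A hospital random intercept lets hospitals differ in level. It does not let them differ in how far they move on the log-odds scale. The intervention is delivered hospital by hospital and is deliberately local, so unequal movement is the natural expectation. Variation in the change between hospitals then belongs in the standard error of the period effect, and this model has no place for it.

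The estimated intercept variance suffers too. It becomes a compromise between clustering within a period and agreement between periods, so it shrinks when hospitals change rank. That carries some of the error into the single-period 2026 rate.

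Interval width matters here. The Sample size section calls the superiority calculation mainly illustrative and gives estimation of national adherence around the 85% target as the aim.

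**Working it through.** **Inputs from the article (Sample size):** 61 hospitals; 35 patients per hospital per period; 10% non-inclusion; rates 10% and 85%; ICC 0.10.

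**Input not in the article:** the correlation ρ between a hospital's effect in 2023 and in 2026. It is assumed and varied from 0 to 1. The random-intercept model corresponds to ρ = 1 with equal variances.

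**Step 1: the plan's own figures.**
- Patients: 2 × 2135 × 0.9 = 3843, so 1921.5 per period and 1921.5/61 = 31.5 per hospital per period.
- Design effect: 1 + (35 − 1) × 0.10 = 4.40.
- 2026 half-width: 1.96 × √(0.85 × 0.15 × 4.40/1921.5) = 3.35 points, against the stated 3.4. The plan's figure is reproduced.

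**Step 2: closed-form variance of the absolute difference** (correlation on the proportion scale, m = 31.5).
- Between-hospital variances: 0.10 × 0.10 × 0.90 = 0.0090 in 2023 and 0.10 × 0.85 × 0.15 = 0.01275 in 2026.
- Within-hospital part: 0.90 × (0.09 + 0.1275)/31.5 = 0.00621.
- Half-width: 1.96 × √{[0.0090 + 0.01275 − 2ρ√(0.0090 × 0.01275) + 0.00621]/61}.
- Results: 4.20 points at ρ = 0, 3.30 at 0.5, 2.74 at 0.75 and 2.03 at 1. The within-hospital part alone gives 1.98.

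This shows how strongly the required width depends on ρ. It does not show what the stated model would report, so the model was fitted to simulated data.

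**Step 3: simulation.** Hospital effects were normal on the logit scale, set to give ICC 0.10 on the proportion scale in each period (SD 1.04 at 10%, 0.92 at 85%), with no covariates. The stated model was fitted by maximum likelihood with Gauss-Hermite quadrature, and the marginal difference was given a delta-method CI. Each setting had 200 to 300 runs, so Monte Carlo error on coverage is about 1.5 to 3 points. Here ρ is on the logit scale, so these widths need not equal those of Step 2. Half-widths are in percentage points.

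| ρ | Stated model: half-width | Coverage | 1.96 × actual SD | Random-slope model | Paired hospital analysis | Log-odds: actual SD / model SE |
|---|---|---|---|---|---|---|
| 0 | 2.5 | 70-76% | 4.4 | 4.1 (91%) | 4.3 (96%) | 1.97 |
| 0.5 | 2.7 | 84-86% | 3.8 | 3.5 (92%) | 3.6 (95%) | 1.51 |
| 0.75 | 2.8 | 92-95% | 3.0 | 3.1 (92.5%) | 3.3 (97%) | 1.27 |
| 1 | 2.9 | 96% | 2.9 | not run | 3.0 (97%) | 1.01 |

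Brackets give coverage. At ρ = 0.6 the stated model covered 87-89%. Bias in the difference was at most 0.1 point, so the shortfall lies in the standard error. At ρ = 0 the widths imply coverage of 2Φ(1.96 × 2.454/4.356) − 1 = 2Φ(1.104) − 1 ≈ 73%, so the 70-76% spread is Monte Carlo error.

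**Step 4: the 2026 rate.** The stated model gives a half-width of about 2.7 to 2.9 points at ρ = 0 to 0.3, where about 3.3 is needed. At ρ = 0.5 it gives 3.0. Coverage was about 89-91% at ρ = 0 to 0.5.

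**Step 5: other settings.** With 10% rising only to 50%, coverage of the difference is 77% at ρ = 0 and 89% at 0.5. With ICC 0.10 read on the latent scale it is 80% and 88%.

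**The case against.** The strongest reply is that this is close to a census. Targeted sites lists 60 of the 62 Dutch hospitals performing ERCP plus one regional hospital, and the limitations box claims all centres that do ERCP for choledocholithiasis. If the target is the realised mean change in these 61 hospitals, variation in change is part of the quantity and not sampling error. In simulation the random-intercept interval covered that target in 98.8-99.2% of runs for ρ from 0 to 0.75 (model SE 1.24 to 1.43 points, actual error SD about 1.0), so it is conservative. This stands for that target. But the plan models hospitals as random and sizes its precision with an ICC, which treats them as a source of uncertainty. The before-after interval should do the same.

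Three further replies have some force.

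- A reader might infer that the model makes every hospital improve by the same number of percentage points, and so contradicts the slope chart. It does not. The common change is in log-odds, and percentage-point changes still vary with the starting level.
- The paired sensitivity analysis does let changes differ and covers well. But it is not adjusted for case mix as described, and it does not supply the primary interval.
- The design effect of 4.40 concerns single-period adherence. It is a yardstick for the 2026 rate (a gap of about half a point), not for the difference.

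The random-effects structure is a stated choice in the article, not a detail left to a fuller document.

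**Conclusion.** The point holds conditionally. If hospitals' log-odds changes differ, and hospitals are treated as a sample as the plan's ICC implies, the primary CIs for the period effect and the absolute difference are too narrow. The 2026 rate is affected to a lesser degree.

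The size rests on the assumed correlation. The loss is serious at 0 to 0.6 and small for the absolute difference at 0.75, although the actual log-odds SD is still 1.27 times the model SE there. It vanishes at 1. The documents do not support a flat statement that the interval is too narrow, because they give neither the correlation nor the spread of changes.

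A reader might also infer that the finding of improvement is in doubt. It is not: against an expected rise of 75 points, an interval that should be about ±4 rather than ±2.5 changes no conclusion about direction. What suffers is the stated precision. Severity: should fix, not must fix.

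**What to change.** In Primary objectives' statistical plan, replace the random-intercept sentence with: *A random intercept and a random slope for period per hospital, with unstructured covariance, will account for clustering and for between-hospital variation in the change.* Derive the marginal rates, the absolute difference and their CIs from that model, and report the between-hospital SD of the change.

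Name a fallback for non-convergence: hospital plus hospital-by-period random intercepts, or the random-intercept model with hospital cluster-robust standard errors.

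The cost is one sentence and one model term, with no extra data or patients. Intervals become somewhat wider (for the difference, ±3.5 instead of ±2.7 points at ρ = 0.5), and convergence may be harder. The richer model is not perfect: its Wald intervals covered 91-93.5% in simulation. At ρ = 0.75 it gains little for the absolute difference.
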